### Patient and public involvement

Patients and the public were not involved in the trial design, and they will not participate in the guidance, or implementation of this study. Once the trial is completed, the results will be disseminated through social media, academic conferences, or research publications.

### Participants and recruitment

There were two ways to recruit patients. One was to display recruitment posters of the study in all participating hospitals. The posters will contain brief descriptions of inclusion and exclusion criteria, the medicines, the ways of participation, and study purposes. Another way is to publish announcements on the hospital’s website. Prior to the start of the trial, all researchers are clinical obstetricians and received formal professional training to do diagnostic interviews. If there were people who were not eligible or refused to participate, we recorded the detailed reasons.

#### Inclusion criteria

Diagnostic criteria are based on the guidelines of the European Society of Human Reproduction and Embryology 2016. Subjects must meet all of the following requirements:
Chinese women aged less than 40 yearsOligomenorrhea/amenorrhea for more than 4 monthsAt least 2 basal FSH level more than 25 IU/L, on two occasions more than 4 weeks apartSign the informed consent

#### Exclusion criteria

Excluded individuals who have met either one of the following criteria:
Patients with serious diseases, such as malignant tumor and thrombosisPatients with severe mental disordersCongenital abnormal development of reproductive organs, or amenorrhea caused by acquired organic lesions and injuriesPeople with chronic diseases that requires hormone therapyPregnant or breastfeeding womenPatients are taking drugs or acupuncture that could affect menstrual cycle or ovarian function, or had participated in another clinical trial in the previous 3 months that could affect the reproductive systemThe patient is allergic constitution or allergic to the study drugsDrink or use drugs

### Removal, dropout, suspension, and termination criteria

During the clinical trial, participants who violate the protocol operation will be removed their participation, for instance, failed to take the drug in accordance with the regulations (medication compliance less than 80%) that affect the judgment of drug efficacy because incomplete data will affect the judgment of efficacy and safety. Participants can voluntarily drop out at any time during the trial. Emergency unblinding or loss of eligible subjects to follow-up will be considered dropping out. If the participant drops out, the last recorded data will be recorded and analyzed. These will be recorded in detail in electronic medical records. If participants have any of the following circumstances, the drug treatment discontinues immediately, while safety or post-treatment visits may continue. These circumstances were (1) a serious adverse event occurred, (2) pregnancy, (3) use of medication that can affect menstrual cycle or ovarian function, (4) the participant withdrew the informed consent form, and (5) the subjects showed hypersensitivity reactions to BSHX, such as stomach pain and diarrhea. Once the blindness is made public, or the opening rate of emergency letters exceeds 20% of the sample size, it means that the double-blind experiment will be invalidated and the entire study will be terminated.

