### Randomization and blinding

The randomization sequence is generated by a computer and randomization numbers are hidden in sealed, opaque, and sequentially numbered envelopes, which are properly kept until the end of the trial. Participants will be randomly assigned (1:1) using a computer-generated randomization sequence to receive oral BSHX or BSHX placebo. The statistician who is not involved in recruiting will prepare the randomization list, and the list will not be available to anyone in any center. Researchers who do not participate in the recruitment label the envelopes. Meanwhile the size, color, taste, and shape of the placebo are consistent with the corresponding drugs, and all study groups assigned by different numbers will use the same packages of medicines. All the documents related to the randomization and allocation sequence generation will be kept in a box in a locked cabinet away from the clinical environments. Packages of BSHX and placebo were provided to randomly assigned two groups of women in each hospital’s centers. This is a double-blind trial, in which all researchers and subjects will be blinded for the treatment allocation until the trial is completed. If there is a serious adverse event or an emergency unblinding event, the blind will be immediately broken.

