### Intervention

All clinics followed the same study protocol. BSHX granules and placebo granules were assigned to different groups for a period of 3 months of treatment. The prescription of placebo is composed of 98% maltodextrin, 2% caramel, and very little bitterant. The BSHX and placebo were manufactured by Jiangyin Tianjiang Pharmaceutical Co. Ltd. (Jiangyin, Jiangsu Province, China) in compliance with China Good Manufacturing Practice standards. Both BSHX and placebo were approved and regulated by the China Food and Drug Administration (FDA) and can be valid for 2 years. The medicines have been widely used in our hospital for many years, and the clinical efficacies were noticeable. Different from other traditional herbs prepared by boiling, it is easier and quicker by dissolving BSHX or placebo (one bag three times a day, 30 g/bag) in water for 30 min. Treatment was taking these medicines after meals three times a day for 3 months. After treatments, medicine packages will be required to return, and compliance will be calculated based on the residual medication. Dosages of Chinese medicines were in accordance with the latest standards of the Chinese Pharmacopoeia (2015 edition). Trial records were confidential and secure.

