### Safety assessments

Studied medicine safety testing includes liver and renal function test, blood routine examination, urine routine examination, stool routine examination, and electrocardiogram. These parameters will be obtained both at screening and after treatment, and all samples were tested by the Jiangsu Province Hospital on Integration of Chinese and Western Medicine in China. Standardized protocols exist at the study center regarding the management of known of potential adverse effects. Adverse events related to the intervention will be monitored through review of the patient’s records, participant self-report, and by the clinicians. All adverse events during treatment and follow-up will be recorded and analyzed in detail. If a participant has a serious adverse event and was not safe to continue the trial, the participants were requested to withdraw from the trial. Immediate relevant treatments were provided to those participants, and following up continued until the response was terminated.

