### Statistical analysis

Data will be analyzed with SPSS V.21 (IBM) by statisticians independent from involved researchers in this study. Efficacy and safety will be evaluated by intention-to-treat (ITT) analysis within the full analysis set (FAS) according to the ITT principle. At the same time, per-protocol (PP) analysis will apply to evaluate data collected from subjects who have completed all steps of the trial protocol. Results of the full analysis set and the per-protocol set will be compared. All prespecified outcomes will analyze in the ITT population because ITT analysis often underestimates the efficacy and was usually conservative. On the contrary, PP analysis overestimates the efficacy and the differences between the two groups. Therefore, this study mainly uses ITT analysis, and PP analysis will be applied if there was a statistical significance. Various assignment methods were used to detect whether the results of different assumptions of missing data are robust. The safety evaluation will be conducted by ITT analysis.

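### Removing randomised women for compliance below 80% conflicts with the stated ITT analysis and leaves open whose CMS data enter the main comparison

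*Protocol article*

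**What the plan says.** The section on removal, dropout, suspension and termination says that "participants who violate the protocol operation will be removed their participation, for instance, failed to take the drug in accordance with the regulations". The threshold and the reason follow directly: "medication compliance less than 80%) that affect the judgment of drug efficacy because incomplete data will affect the judgment of efficacy and safety". The Intervention section fixes when this can be known: "After treatments, medicine packages will be required to return, and compliance will be calculated based on the residual medication".

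The removal section treats drop-outs separately. "Emergency unblinding or loss of eligible subjects to follow-up will be considered dropping out", and for this group it adds: "If the participant drops out, the last recorded data will be recorded and analyzed". It has no matching sentence for removed women.

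The sample size section starts from about 70 per arm. It then allows for protocol violations and for drop-out of at most 15%, so that enough participants remain for the efficacy analysis.

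The statistical analysis section says "All prespecified outcomes will analyze in the ITT population". It makes ITT the main analysis, adds a per-protocol analysis, and mentions several imputation methods to test robustness to missing data. The abstract has the CMS measured in all participants at baseline, month 3 and month 6.

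Three statements bear on follow-up after a serious adverse event:
- The removal section stops study drug and allows safety or post-treatment visits to go on.
- The blinding section says "If there is a serious adverse event or an emergency unblinding event, the blind will be immediately broken".
- The safety section says that, where it was not safe for the woman to go on, "the participants were requested to withdraw from the trial", with follow-up until the event has ended.

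**The concern.** A compliance threshold justified by its effect on judging efficacy is a per-protocol criterion, and the plan already has a per-protocol analysis to hold it. Here it is written as removal from the trial. Compliance is observed after randomisation and may depend on tolerability or on perceived benefit. If it decides whose CMS is available or used, the groups compared are no longer those formed by randomisation, and the main analysis may be ITT in name only.

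The question also stays open until late. Compliance is calculated at about the time the month-3 CMS is due, so who counts in the main comparison could be settled after compliance, and perhaps outcomes, are known.

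A related weakness concerns drop-outs. With so few CMS assessments, analysing the last recorded value will often mean analysing baseline.

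**Working it through.** **1. The plan's own figure.** The plan gives no rate of removal for non-compliance. The nearest figure is the 15% drop-out allowance, with violations mentioned beside it but given no rate. Two arms of 70 make 140, and 140/0.85 = 164.7, so the stated 148 is not reproduced. That is a separate matter. What counts here is that violators are treated as losses from the efficacy analysis, which they would not be under ITT.

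**2. Timing.** The CMS is due at months 0, 3 and 6. Treatment ends at month 3, and compliance is calculated from packs returned afterwards. For a woman removed on that count there are two possibilities:
- Her month-3 CMS exists and is set aside. This changes the comparison of groups at months 0 and 3.
- Her month-3 CMS is kept but follow-up ends. The month-6 CMS is then missing, which affects the repeated-measures analysis across the trial but not the month-3 comparison.

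Neither fits analysis of all prespecified outcomes as randomised. Other violations, found earlier, could also cost the month-3 value.

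**3. Drop-outs, including emergency-unblinded women.** Their last recorded value is analysed. Before month 3 the only CMS on record is baseline, so change = baseline − baseline = 0. Such a woman is counted, but as having had no change.

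**4. Possible size of selection bias.** Inputs from the sample size section are SD 7.42 and target effect 2.9. Assumptions not in the documents are the fraction f removed and the correlation c between the tendency to be removed and poor response. With normal outcomes, no true effect and removed women left out of the analysis, the arm mean shifts by

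shift = c × SD × φ(z_f) / (1 − f),

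where φ is the standard normal density and z_f the point that cuts off fraction f. φ(z_f) is 0.1755 for f = 0.10 and 0.2332 for f = 0.15.

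| f, one arm only | c | Shift (CMS points) | Share of 2.9 |
|---|---|---|---|
| 0.10 | 0.3 | 0.3 × 7.42 × 0.1755/0.90 = 0.43 | 15% |
| 0.15 | 0.3 | 0.3 × 7.42 × 0.2332/0.85 = 0.61 | 21% |
| 0.10 | 0.5 | 0.5 × 7.42 × 0.1755/0.90 = 0.72 | 25% |
| 0.15 | 0.5 | 0.5 × 7.42 × 0.2332/0.85 = 1.02 | 35% |

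When women are removed from both arms, only the difference between the shifts remains. With 15% against 10%, taking unrounded values, it is 0.18 points (c = 0.3) to 0.29 points (c = 0.5), or 6 to 10% of 2.9. With equal removal in both arms, or c = 0, it is zero.

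**The case against.** The best defence is that removal is from participation, not expressly from analysis. The statistical section names ITT as the main analysis, keeps per-protocol apart and plans sensitivity analyses for missing data. An exact definition of the full analysis set may stand in an analysis plan that is not shown. This is fair as far as it goes: exclusion from the main analysis is an inference, not a stated rule. It does not remove the conflict, because the sample size section counts violators as lost to the efficacy analysis and only drop-outs are said to have their data analysed.

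A reader might infer more, but the documents do not support it:
- **That emergency-unblinded women are excluded.** They are classed as drop-outs, and the next sentence has drop-outs' last recorded data analysed.
- **That removed women have no month-3 or safety data, so ITT is impossible.** Compliance is calculated at about month 3, when the CMS and the after-treatment safety tests are due. The safety section records and analyses all adverse events, and safety is evaluated by ITT.
- **That the removal and safety sections flatly contradict each other on serious adverse events.** The request to withdraw covers only women for whom continuing was not safe, and they are followed until the event ends. Unclear is the better word.
- **That any bias favours BSHX.** The placebo is matched for taste, and lack of benefit could remove more women from the placebo arm. Stomach complaints, which the protocol names as reactions to BSHX, could act the other way.

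**Conclusion.** The point holds as a conflict within the text. A per-protocol criterion, measured after randomisation, is written as removal from the trial, while the main analysis is declared to be ITT. Who contributes to the main comparison is therefore not settled.

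The documents give neither the direction nor the size of any bias. The 0.4 to 1.0 points is an illustration that rests on assumed removal in one arm only, assumed correlations, and removed women being left out. It shrinks quickly once both arms lose women. The drop-out rule is a lesser fault: it keeps unblinded women in the sample, but those who leave before month 3 enter as unchanged from baseline.

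**What to change.** - Use the 80% compliance threshold only to define the per-protocol set, and delete it as a ground for removal from the trial.
- Separate stopping study drug from leaving the study. Women who are non-compliant, off drug or unblinded, and who have not withdrawn consent, are still asked for the month-3 and month-6 CMS and are analysed as randomised with all data collected.
- Name a primary method for missing CMS values that does not rest on carrying the last (often baseline) value forward.
- Reconcile the removal, blinding and safety sections on what follow-up takes place after a serious adverse event.

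The cost is wording, a few more questionnaires and some analysis work. The trial status section expected follow-up to finish by the end of November 2021, so some questionnaires may no longer be obtainable. The analysis rules can still be fixed if the blind has not been broken.

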### Sample size calculation

Sample size estimation refers to the calculation of the required sample size in order to meet the accuracy and reliability of statistics (the control of type I errors and the guarantee of inspection efficiency) [21]. The sample size of this study was based on the relevant literature reviews and the validity of hypotheses. The main indicator of this study is to detect the difference of the total score (CMS) between the two groups before and after treatment. There is one randomized clinical trial for BSHX in the treatment of POI [13]. However, there is no placebo control group in the clinical trial and the primary outcome measurements were different. Thus, the parameters are not suitable to estimate the sample size of the trial. We referred to other clinical trials of traditional Chinese medicine in the treatment of POI patients [22]. We assumed that BSHX administration would reduce CMS score by 2.9 points and the SD is 7.42 in the study [23]. If a type I error rate of *α* = 0.05, a power of 90 % (type II error rate of *β* = 0.1), then u1 − *α* =1.64, u1 − *β* =1.28. n1 = n2 ≈ 70. During the 3-month treatment period, taking into account the possible protocol violations, and the maximum possible drop-out rate of 15%, we need 148 participants in total to achieve the number of people required for the efficacy analysis. One hundred fifty participants will be recruited for this study, and the following formula was used to estimate the sample size:
$$ n=2\times {\left[\frac{\left({z}_{1-\raisebox{1ex}{$\partial $}\!\left/ \!\raisebox{-1ex}{$2$}\right.}+{z}_{1-\beta}\right)\sigma }{\delta}\right]}^2 $$

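### The rule that removes women below 80% compliance conflicts with the ITT main analysis and with CMS follow-up of all participants, and leaves their data without a stated rule

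*Protocol article*

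**What the plan says.** All places are in the protocol article.

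- **Removal, dropout, suspension, and termination criteria.** "participants who violate the protocol operation will be removed their participation, for instance, failed to take the drug in accordance with the regulations". The example is "medication compliance less than 80" per cent, and the reason given is "because incomplete data will affect the judgment of efficacy and safety". For dropouts the section adds: "If the participant drops out, the last recorded data will be recorded and analyzed". It separately allows visits to go on after study drug is stopped for five listed events. Poor compliance is not one of the five.
- **Intervention.** "After treatments, medicine packages will be required to return, and compliance will be calculated based on the residual medication". No earlier compliance count is described.
- **Statistical analysis.** "Efficacy and safety will be evaluated by intention-to-treat (ITT) analysis within the full analysis set (FAS) according to the ITT principle". All prespecified outcomes are assigned to the ITT population. A separate per-protocol analysis covers women who completed every step, and several ways of filling in missing data are planned as a robustness check.
- **Abstract, Methods and design.** CMS is measured at baseline, month 3 and month 6 in every participant.
- **Sample size calculation.** The inflation of the sample size is explained by "taking into account the possible protocol violations, and the maximum possible drop-out rate of 15" per cent, in order to reach the number needed for the efficacy analysis.

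**The concern.** ITT requires women to be followed and analysed as randomised, whatever they took. A rule that ends participation because of low intake works against this. It also duplicates the per-protocol set, which is where a compliance threshold belongs. The stated reason is partly circular, since ending participation itself makes the data incomplete.

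Compliance is observed after randomisation. Taking three 30 g bags a day for 3 months may depend on perceived benefit and on tolerability, and either may differ by arm. If women who do poorly are lost at different rates, or for different reasons, in the two arms, the remaining groups are no longer comparable. The primary outcome is a self-reported score, so such selection could shift the main result.

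**Working it through.** **Step 1: what happens to the data of a removed woman**

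| Provision | Applies to | Stated for women below 80%? |
|---|---|---|
| Last recorded data analysed | Dropouts | No |
| Visits may continue | Five drug-stopping events | No |
| ITT within FAS | All prespecified outcomes | Yes by principle, but the removal rule works against it |
| CMS at months 3 and 6 | All participants | Yes by wording, but not possible after participation ends |

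Extending the last-recorded-data rule to these women would help little. CMS is measured only at months 0, 3 and 6, so the value carried forward is the baseline or the month-3 score.

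**Step 2: timing**

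Packs are returned and counted after treatment, so on the text the rule acts at about month 3 or later.

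- If the month-3 CMS is taken and kept, the loss is the month-6 CMS and later follow-up. The planned repeated-measures ANOVA of CMS, in its standard form, uses complete cases. A missing month-6 score can then remove a woman's earlier scores as well, unless it is imputed.
- If removal is applied as an analytic exclusion, or non-compliance is acted on earlier, the month-3 CMS is lost too.

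**Step 3: how large a bias could be (illustration, worst reading)**

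The article has no figure of its own to reproduce on this point: it gives no expected compliance rate and no link between compliance and CMS.

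From the article: SD 7.42, target difference 2.9 points, 150 women allocated 1:1 (75 per arm).

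Assumed: no true effect; removed women fully excluded; fraction p removed in an arm; correlation ρ between a poor CMS result and the tendency to be removed; two-sided 5% test.

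Shift in the mean of the retained women in one arm = ρ × SD × φ(c) / (1 − p), where c is the standard normal quantile at 1 − p and φ is the normal density. Bias is the difference between the two arms' shifts. Approximate SE = 7.42 × √(1/n₁ + 1/n₂), with n₁ and n₂ the retained numbers. Type I error ≈ P(Z > 1.96 − bias/SE) + P(Z < −1.96 − bias/SE).

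- **Same rate and same link in both arms** (15% each, ρ = 0.5): each shift is 0.5 × 7.42 × 0.2332 / 0.85 = 1.02. The difference is 0 and type I error stays at 5%.
- **Same link, unequal rates** (ρ = 0.5, 20% v 10%): 0.5 × 7.42 × 0.2800 / 0.80 = 1.30 and 0.5 × 7.42 × 0.1755 / 0.90 = 0.72. Bias is 0.58 point. With 60 and 67.5 retained, SE = 1.32, bias/SE = 0.44 and type I error is about 7%.
- **Selection on outcome in one arm only** (15% removed in each arm, ρ = 0.5 in one and 0 in the other): bias is 1.02 − 0 = 1.02 points, or 35% of 2.9. With 63.75 retained per arm, SE = 1.31, bias/SE = 0.77 and type I error is about 12%.

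Simulations of a t-test on retained women agree: type I error of about 5%, 7% and 12-13% in the three cases.

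**Step 4: cross-check with a simpler model**

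Bias = (difference in removal rates) × (how much worse removed women score than retained women). Assume a gap of 3.71 to 7.42 points (0.5 to 1 SD). Removal of 15% v 5% gives 0.10 × 3.71 = 0.37 to 0.10 × 7.42 = 0.74 point. Removal of 25% v 5% gives 0.74 to 1.48 points. Equal removal with an equal gap gives none.

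**The case against.** The strongest reply is that the rule speaks of participation and not of the full analysis set. A woman can stop attending and still be counted under ITT with missing values, and the article plans sensitivity analyses for missing data. Her month-3 CMS may already exist when packs are counted, and the explicit between-arm t-test is at month 0 and month 3. All of this stands. It means that loss of the primary month-3 result is possible but not stated. It does not settle what is done with these women, and sensitivity analyses do not replace data that could have been collected.

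The interviews every 2 weeks could reveal poor compliance earlier. That is also fair, but earlier removal would cost more data. The allowance in the sample size section may have been meant to protect the per-protocol set; the wording allows either reading.

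Two stronger readings are tempting and not supported. A reader might infer that the rule biases the result towards BSHX. The article gives no compliance rates by arm. Under matched placebo, women without benefit on placebo could equally be the less compliant group, which would reverse the sign, and identical removal in both arms gives no bias. A reader might also infer that women with complaints drop out of the safety evaluation. Serious adverse events and hypersensitivity reactions have their own route with continued visits, all adverse events in treatment and follow-up are to be recorded, and safety is evaluated by ITT. Any safety loss is therefore partial.

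**Conclusion.** The point holds as a conflict between stated rules. Ending participation for compliance below 80% does not fit an ITT main analysis or CMS at months 3 and 6 for all, and no data rule is stated for the women affected. The clearest loss is the month-6 CMS and later follow-up; the month-3 CMS is at risk only if removal comes earlier or is applied as an analytic exclusion.

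The loss is avoidable and may be related to outcome, so it can bias the comparison. Its size and direction cannot be known from the article. The illustrative range, from no bias to about 1.0 point with 12-13% type I error, rests on full exclusion of removed women and on assumed removal rates and correlations. It shows what could be at stake and is not an estimate for this trial.

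**What to change.** Reconcile the removal criteria, the Statistical analysis section and the Sample size calculation:

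1. State that non-compliance does not end data collection. Every randomised woman who has not withdrawn consent is asked to complete CMS at months 3 and 6 and the safety assessments.
2. State that all randomised women stay in the full analysis set in their randomised arm, whatever their compliance.
3. Use compliance below 80% only to define the per-protocol set, and fix that set in a blinded review before the code is opened.
4. Let the 15% allowance refer to missing CMS in the ITT analysis, not to protocol violations.

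This concerns data collection and analysis sets only and leaves the rules on study drug untouched. The cost is a wording change plus continued follow-up of a few women. The ITT estimate will include non-compliers and may be slightly smaller.

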**Methods and design:**

We plan to recruit 150 women with POI from four participating hospitals in China. Participants will be randomized in a 1:1 to receive oral BSHX or BSHX placebo. All participants will be treated for 3 months and will be followed up for another 3 month. The primary outcome is questionnaire scores based on the changes in the total symptoms, which is the Chinese version of the Menopause-Specific Quality of Life (CMS) (Nie G, Yang H, Liu J, Zhao C, Wang X, Menopause 24(5):546–554, 2017). CMS will be measured before the intervention, at 3 months and 6 months after randomization for all participants. The other measurements include serum sex hormone levels, anti-Müllerian hormone (AMH) levels, ovarian peak systolic velocity (PSV; cm/s), and antral follicle count (AFC). In this study, the regulatory effects of traditional Chinese medicine on hormones were evaluated by the changes of serum sex hormone levels, which include serum estradiol (E2), luteinizing hormone (LH), and follicle-stimulating hormone (FSH). These indicators will be measured before intervention and at 3 months after randomization.

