### Follow-up

All included patients will be re-evaluated at 2, 4, 6, 8, 10, 12, 16, 20, and 24 weeks’ follow-ups. Wherever in-person follow-up was not possible, video conferencing or telephone follow-up was carried out.

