### Outcome measures

#### Primary outcome

The primary outcome measurement was the CMS questionnaires. The CMS was translated by Yang Hongyan and others [24]. In clinical practice, the Chinese version of the MENQOL Questionnaire (Table S3 in supplementary materials) has been proven to be highly reliable, effective, and responsive. It is a reasonable and effective tool to comprehensively evaluate the current physical and mental health problems of menopausal women in China [25]. CMS has a total of 29 items, which are divided into 4 dimensions, including vasomotor symptoms (3 items), psychosocial symptoms (7 items), physiological health (16 items), sexual health-related questions (3 items). Differences in this questionnaire are that MENQOL appears not only as symptoms based on the frequency, it also includes the troubles caused by various severity of symptoms degree. Participants will complete the questionnaires before, after the intervention, and follow-up. Items measured and data collection schedule are shown in Table S4 (in supplementary materials).

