Descriptive analysis will be used for baseline variables including demographic characteristics, medical history, course of disease, treatment history, combined diseases, concomitant medications, vital signs, laboratory tests for safety assessment, and adverse events. Continuous variables will be expressed by mean ± SD; categorical variables will be shown as counts and percentages. Estimates of the adjusted differences in risks are presented with 95% confidence intervals (CIs) of the difference. The comparability of the characteristics between the BSHX and placebo groups will be assessed by using *t*-test for continuous variables with normal distribution, while the non-parametric Mann-Whitney-Wilcoxon test will be used for the comparison of data with non-normal distribution. Specifically, the paired *t*-test will be used to compare the difference of the outcome between preintervention and postintervention in each group and independent t-test will be used to compare the difference between the two groups. Categorical variables will be compared using *Χ*^2^ statistics, while the Fisher exact test will be used when the theoretical frequency is less than 5 in more than 25% of the cells. In order to control the center and baseline effects, covariance analysis will be applied for the intergroup comparison with continuous variables and Cochran-Man-tel-Haenszel test for categorical variables. The differences of CMS scores, levels of FSH, LH, E2, AMH, the AFC, and ovarian PSV (cm/s) at month 0 and month 3 between the BSHX and placebo groups will be compared using an independent *t*-test. A repeated-measures analysis of variance (ANOVA) test with Bonferroni post hoc test will be used to evaluate the changes in CMS scores, levels of FSH, LH, E2, AMH, the AFC, and ovarian PSV (cm/s) and safety assessment measurements throughout the experiment. In all tests, a value of *p* < 0.05 will be considered statistically significant. All statistical analyses will be performed using SPSS V.20.0.

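### Read naturally, the rule for drop-outs puts the baseline CMS score in place of a missing month-3 score; this can bias the effect in either direction and overstate its precision

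*Protocol article*

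**What the plan says.** The rule is in the Protocol article, under the criteria for removal, dropout, suspension and termination: "If the participant drops out, the last recorded data will be recorded and analyzed". The same section defines the group widely: "Emergency unblinding or loss of eligible subjects to follow-up will be considered dropping out", in addition to voluntary withdrawal.

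The abstract gives the CMS schedule: "CMS will be measured before the intervention, at 3 months and 6 months after randomization for all participants". The Primary outcome section agrees: "Participants will complete the questionnaires before, after the intervention, and follow-up". The Follow-up section lists more frequent contacts ("All included patients will be re-evaluated at 2, 4, 6, 8, 10, 12, 16, 20, and 24 weeks’ follow-ups") but does not say that CMS is completed at them. The schedule table (Table S4) is supplementary and not shown.

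The Statistical analysis section compares CMS and the secondary measures "at month 0 and month 3 between the BSHX and placebo groups will be compared using an independent" t-test, and also foresees covariance analysis for centre and baseline. On populations it says "Therefore, this study mainly uses ITT analysis, and PP analysis will be applied if there was a statistical significance". On missing data it adds only "Various assignment methods were used to detect whether the results of different assumptions of missing data are robust", and it names none of these methods.

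**The concern.** Put together, these statements lead to one result. If the last recorded value is what gets analysed, all randomised women count in the main analysis, and no CMS is taken between baseline and month 3, then a woman lost during treatment has only her baseline score to contribute. Her change is set to zero.

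Two things follow. First, whatever change she would have shown, including any improvement that also occurs on placebo, is erased, and erased more often in the arm that loses more women. Second, the t-test counts each zero as a measured outcome with no uncertainty. The primary estimate, its confidence interval and, under unequal loss, the false-positive rate are all at stake. The Statistical analysis section justifies ITT as usually conservative, but this rule is not reliably so.

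**Working it through.** The plan gives no figure for the effect of this rule, so there is none to reproduce.

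**Inputs from the document.** From Sample size calculation: difference d = 2.9, SD s = 7.42 (s² = 55.06), drop-out up to 15%, 150 women. With 1:1 allocation that is 75 per arm.

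**Assumptions not in the document.** 7.42 is the SD of the change. Drop-out is unrelated to outcome, and women lost would have had the full effect of their arm. The mean improvement on placebo is P. The split of drop-out between the arms is pA on BSHX and pP on placebo. Improvement is written as a positive number.

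**Formulas, with a zero change for each woman lost.**
- Expected difference: (1 − pA)(P + d) − (1 − pP)P.
- Variance of change in an arm with mean m and loss p: (1 − p)s² + p(1 − p)m².
- Reported SE: √[(variance on BSHX + variance on placebo)/75].

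**1. Equal loss, 15% in each arm.**
- Difference: 0.85 × 2.9 = 2.465, whatever P is.
- SE with P = 0: √[(47.87 + 46.80)/75] = 1.12.
- SE with P = 5: √[(54.76 + 49.99)/75] = 1.18.
- SE from observed women only: 75 × 0.85 = 63.75 per arm, so 7.42 × √(2/63.75) = 1.31.
- The reported SE is thus about 10% to 15% too small over this range of P. With P = 10 it rises to 1.30 and the gap almost closes.

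**2. Unequal loss, true effect 2.9, P = 5.**
- 20% lost on BSHX, 10% on placebo: 0.80 × 7.9 − 0.90 × 5 = 6.32 − 4.50 = 1.82.
- 10% lost on BSHX, 20% on placebo: 0.90 × 7.9 − 0.80 × 5 = 7.11 − 4.00 = 3.11.

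**3. No true effect.** The expected difference is P(pP − pA). The type I error is Φ(t − 1.96) + Φ(−t − 1.96), where t is that difference divided by its SE.

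| Loss BSHX / placebo | P | Spurious difference | SE | Two-sided type I error |
|---|---|---|---|---|
| 15% / 15% | 5 | 0 | 1.15 | 5.0% |
| 10% / 20% | 2.9 | 0.29 | 1.13 | 5.8% |
| 10% / 20% | 5 | 0.50 | 1.15 | 7.2% |
| 10% / 20% | 8 | 0.80 | 1.21 | 10.2% |

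Simulating 40,000 null trials with random losses of 10% and 20% gave 7.4% at P = 5 and 10.1% at P = 8, which agrees with the formula.

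**The case against.** A reader might infer that the protocol prescribes last observation carried forward as its primary method. The text does not go that far. The sentence stands among the withdrawal criteria, not in the Statistical analysis section; it names no method and does not say that a value replaces a missing month-3 score. It could mean only that data collected before drop-out are kept. That reading is possible but less natural, because the sentence says the last recorded data are analysed and the article offers no other primary handling. The robustness checks are unnamed and, as worded, test a result that must already come from some method.

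A reader might also infer that every drop-out contributes a baseline score. That is not established. Table S4 could contain a CMS at withdrawal. The withdrawal criteria allow visits to continue after treatment stops, so stopping treatment need not mean a missing month-3 score. The full analysis set is not defined here; if it required a post-baseline score, the substitution would not arise. Even so, the abstract and the Primary outcome section state no other CMS time point.

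Nor do the documents support a general claim of inflated false positives. Inflation needs both an improvement on placebo and unequal loss. Neither is given, and 20% in one arm exceeds the 15% maximum planned, although 10% and 20% average to it. With equal loss and no effect the test keeps its 5% level. The dilution to 2.5 presumes that women lost would have had the full effect. These limits bear on certainty and size; they do not remove the problem.

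**Conclusion.** The concern holds as a matter of the most natural reading. A woman lost before month 3 would count as unchanged, and that zero would be analysed as if measured. At the planned maximum drop-out, split equally, the effect shrinks by 15% and the standard error looks up to about 15% smaller than the observed data support. Under the assumed imbalances and 5 points of placebo improvement, a true 2.9 becomes 1.8 or 3.1. With no true effect, the type I error is about 7% at 5 points of improvement and about 10% at 8 points. The direction of the bias therefore depends on which arm loses more women and on how much placebo recipients improve, and neither is known in advance. The conclusion is limited to the month-3 outcome.

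**What to change.** Replace the last-recorded-data rule as the primary handling, and state the replacement in the Statistical analysis section:

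- Seek the month-3 CMS at the visit already planned for week 12, in person or by the video or telephone route that the Follow-up section allows, from women who have stopped treatment and have not withdrawn consent.
- For scores still missing, use multiple imputation by arm followed by the month-3 ANCOVA with baseline CMS and centre. Alternatively, use a likelihood-based mixed model with baseline CMS as one of the responses. A mixed model with baseline only as a covariate would drop women who have no later score.
- Add one named sensitivity analysis that departs from missing at random, either delta-adjusted or reference-based. These are different methods, so specify which.
- Keep carry-forward, if wanted, only as a labelled sensitivity analysis.

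The cost is slightly more analysis work, some effort to reach women who stopped treatment, and a somewhat larger but honest standard error.
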